### **12.2 Informed Consent Forms**

All potential participants will be adults (65 years of age or older) who are capable of providing direct consent for their participation in the study. Written informed consent will be obtained at the clinic screening visit prior to performing any of the clinic screening procedures. One of the study investigators will explain the study and the participant will be given a copy of the consent form to read. The consent form will describe the purpose of the study, the procedures to be followed, and the risks and benefits of participation. The investigator will answer any questions that the participant may have about the study. Finally, the participant will be asked to sign and date the consent form. The participant will be given a copy of the consent form for their records.

### **12.3 Participant Confidentiality**

Participant privacy will be protected throughout the research process. Research assessments and interventions are conducted in the PT-CTRC located in the Bridgeside Point Building at the University of Pittsburgh. This space includes several small rooms that can be used to privately conduct questionnaires and simple physical examination measures. Many of the walking assessments are done in the open area of the center, which includes the oval track, the computerized walkway system and treadmills. Participants may be screened individually, which further protects their privacy. Participants are informed via the consent process that the treatment programs may be conducted in small groups. Although not completely private, this level of exposure to others during exercise is similar to what one might experience at a physical therapy appointment or during an exercise routine at a public gym. This research will not involve the use or disclosure of existing identifiable medical information, such as personal medical or hospital records.

Participants' confidentiality will be protected in the data collection process. Consent forms and data collection forms that identify the participant by name will be stored in a locked cabinet. All computers are password protected. If the data are used in scholarly presentations or journal articles, the investigators will protect the anonymity of individual participants and will report only aggregate data (eg group means) where appropriate. The Principal Investigator will review data confidentiality processes monthly or as indicated with the project staff (Study coordinator and Physical Therapists). The Investigators are all certified in Research Practice Fundamentals, Human Subjects Research Module.

### **12.4 Study Discontinuation**

The study may be discontinued at any time by the IRB, the NIA, the OHRP, or other

government agencies as part of their duties to ensure that research participants are protected.

### **13 PUBLICATION OF RESEARCH FINDINGS**

Publications will be operationally defined as manuscripts for publications; abstracts for platform or poster presentation at scientific meetings and other professional meetings; slides for presentation at scientific and other meetings; doctoral dissertations; and master's theses.

The goal of the publication policy is to encourage and facilitate publication of study results. The purposes of this policy are to ensure the following:

- PRIMA publication will be of the highest scientific quality
- PRIMA will be described in a consistent manner across publications
- Measures are reported in consistent ways across publications
- Proper acknowledgements are included
- Appropriate authorship credit is determined prior to submission of manuscripts for publication consideration.

Publications from PRIMA will be overseen by the PI and Co-Investigators.

### **14 ANCILLARY STUDY POLICIES**

An ancillary study will be defined as a study that (1) uses supplementary data that will be collected on participants who are recruited in PRIMA, over and above the data collection required by the PRIMA protocol, (2) collects biological specimens (e.g. blood) or performs diagnostic tests (e.g. bone density scans); and/or (3) collects data on subjects not enrolled in PRIMA but who may be compared to PRIMA subjects (e.g. participant who receive an alternative intervention). Ancillary studies will be distinct from databank studies, which use data previously collected on participants who are enrolled in PRIMA.

Ancillary studies will be reviewed and approved by the PI and CO-I's prior to initiation to ensure they do not conflict with the main study protocol. All approved ancillary studies will also be reviewed by the DSMB and NIA prior to initiation. If approved, the ancillary study PI will report to the DSMB on the same schedule as the main study. Review by the PI and Co-I's will also be required for presentation or publication of ancillary study results.

PRIMA investigators will be encouraged to consider ancillary studies and to involve other investigators, within and outside of PRIMA personnel. Participation in an ancillary study will be subject to approval by the PI, Co-I's and DSMB. The following factors will be considered in determining approval of the proposed ancillary study:

1. Participant burden

- a. The proposed study must be acceptable to the participants (e.g. in terms of time, discomfort, privacy, etc).
  - b. The proposed study must not reduce enrollment or hamper continued participation in the main study.
2. Study interference
  - a. The proposed study must not interfere with the other parts of the main study.
  - b. The proposed study must put little to no additional demands on the PRIMA resources.
3. The proposed study must be of the highest scientific merit.
4. The investigators must have adequate resources to effectively complete the ancillary study including:
  - a. Sufficient budget
  - b. Staff having the required expertise to meet the objectives of the project.

**Supported by:**

**The National Institute on Aging**

**AG045252**

# TASK SPECIFIC TIMING AND COORDINATION EXERCISES TO IMPROVE MOBILITY IN OLDER ADULTS

## PROTOCOL (Version 1.4)

### Summary of Modifications to Protocol Version 1.2 for Version 1.3

| Version
(date)          | Section | Brief Summary of Modification                                                                                                                                                                                                                              |
|----------------------------|---------|------------------------------------------------------------------------------------------------------------------------------------------------------------------------------------------------------------------------------------------------------------|
| Version 1.1
(2/9/2016)  | 4.1     | Removed inclusion criteria #5 – Not meeting physical activity recommendations defined as reporting less than 150 minutes of moderate intensity activity per week in the past month. This question will remain on phone screen so we can track information. |
| Version 1.2
(3/15/2016) | 5.4     | Updated strength training description—all subjects will completed hip extension and abduction strengthening as well as 1-2 other LE strengthening exercises at the PTs discretion                                                                          |
| Version 1.2
(3/15/2016) | 6.1     | Changed timepoint for “medical clearance to participate” to clinic screen; removed CHAMPS questionnaire; added Life Space Assessment and Pitt Sleep Quality Index for baseline, 12 week, 24 week, and 36 week timepoints                                   |
| Version 1.2
(3/15/2016) | 6.2.3   | Removed CHAMPS; added Life Space Assessment                                                                                                                                                                                                                |
| Version 1.3
(6/6/2016)  | 5.6.2   | Changed monthly phone calls to monthly check ins to be documented by study coordinator                                                                                                                                                                     |
| Version 1.3
(6/6/2016)  | 5.7     | Updated requirements for schedule intervention visits to include first session 8-14 days after baseline testing; added randomization timing to details                                                                                                     |

### Summary of Modifications to Protocol Version 1.3 for Version 1.4

| Version
(date)          | Section | Brief Summary of Modification                                                                                                                    |
|----------------------------|---------|--------------------------------------------------------------------------------------------------------------------------------------------------|
| Version 1.4
(8/19/2016) | 8.5-8.7 | Updated information on who RAEs should be reported to and in which order. SAEs that are not related to the protocol will not be considered RAEs. |
|                            |         |                                                                                                                                                  |
|                            |         |                                                                                                                                                  |
|                            |         |                                                                                                                                                  |
|                            |         |                                                                                                                                                  |
|                            |         |                                                                                                                                                  |
|                            |         |                                                                                                                                                  |

## PRÉCIS

### Study Title

Task Specific Timing and Coordination Exercise to Improve Mobility in Older Adults

**Objectives.** The primary objective of the proposed project is to evaluate the impact of adding timing and coordination training to standard strength and endurance training on mobility. Secondary objectives include examining 1) additional outcomes representing the components of the intervention and measures of activity and participation, 2) the delayed and sustained effects of the intervention, and 3) the effects of the intervention within various other subgroups of interest.

**Design and Outcomes.** This is a 5 year randomized single-blind two arm intervention trial to compare the effects on mobility, activity and participation of a standard strength, endurance, and flexibility program to the standard plus timing and coordination program in 248 community-dwelling older adults walking slower than the desired gait speed of 1.2 m/s. Exercise sessions are twice weekly for 12 weeks. Participants are assessed at baseline, 12 weeks (post intervention), 24 weeks and 36 weeks. The primary, secondary, and tertiary outcomes are conducted by assessors masked to group assignment. The primary outcome is gait speed. Secondary outcomes of maximum voluntary isometric contraction of the quadriceps femoris, Six minute walk test, Chair Sit-and-Reach Test, Smoothness of walking, and Gait variability represent the components of the intervention (i.e. strength, endurance, flexibility and timing and coordination). Tertiary outcomes represent measures of activity (Late Life Function and Disability Instrument – function subscale and confidence in walking) and participation (Late Life Function and Disability Instrument – disability subscale and daily physical activity).

**Interventions and Duration.** Intervention sessions are twice weekly for 12 weeks supervised by a physical therapist. All sessions last about 50-65 minutes and include a warm-up, 40-55 minutes of exercise, and a cool down period. Both intervention groups will also receive physical activity behavioral change intervention. The Standard Intervention includes a brief warm-up period, lower extremity strength training, endurance training, and a brief cool down period. The Standard-Plus Task Specific Timing and Coordination Intervention or Standard-Plus intervention includes all components of the Standard Intervention plus task specific timing and coordination training. The total intervention time will be equal between the two intervention groups.

**Sample Size and Population.** The target sample is community-dwelling older adults who walk faster than 0.60 m/s and slower than the desired gait speed of 1.2 m/s. We plan to enroll approximately 124 subjects who walk slowly (i.e. gait speed  $> 0.60$  and  $< 1.0$  m/s) and approximately 124 faster walkers (i.e. gait speed  $\geq 1.0$  and  $< 1.20$  m/s) for a total of 248 subjects. Within each baseline gait speed stratum we plan to randomize individuals to each of the treatment arms so that the gait speed strata are equally represented in each of the arms. Persons who are unable to participate in testing, have medical conditions which would make testing or participation in an exercise program unsafe, or who have plans to permanently leave the area during the study are excluded.

## 1 STUDY OBJECTIVES

### 1.1 Primary Objective

**To determine if a standard-plus program is more successful in improving walking ability (i.e. gait speed) at 12 weeks after study entry compared to a standard exercise program.** *Compared to participants receiving the standard program, participants receiving the standard-plus program will have greater gains in gait speed at 12 weeks after study entry (Hypothesis 1.1); and differences in gains between the programs will occur in both slower ( $<1.0$  m/s) and faster ( $\geq 1.0$  m/s) walkers (Hypothesis 1.2).*

### 1.2 Secondary Objectives

**To assess the effect of the interventions on secondary and tertiary outcomes that represent the main components of the intervention and measures of activity and participation.** *Compared to participants receiving the standard program, participants receiving the standard-plus program will have greater gains in timing and coordination (smoothness of walking, gait variability), activity (Late Life Function and Disability Instrument - function), and participation (Late Life Function and Disability Instrument-disability and physical activity as measured by Actigraph accelerometer) at 12 weeks after study entry; gains in strength (leg press strength and power), endurance (Six Minute Walk Test) and flexibility (Chair Sit-and-Reach) will be similar between the two active treatment groups.*

**To determine if walking ability, secondary, and tertiary outcomes differ between standard-plus and standard intervention groups after a delay and are sustained over a period of time.** *Compared to the participants receiving the standard program, participants receiving the standard-plus program will have greater gains at 24 (delayed effect) and 36 weeks (sustained effect) post randomization.*

**To explore the effects of the interventions on outcomes within various other subgroups of interest (i.e. baseline confidence, physical activity and cognition subgroups).**

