## **5.5 Standard-Plus Intervention (include progression and modifications)**

In addition to the Standard Intervention described above the subjects receiving the Standard-Plus Intervention will complete task specific timing and coordination training. In order to keep the total intervention time equal and the time spent in walking/standing activities equal, the subjects in the Standard Plus intervention complete a 5 minute warm-up, 10-15 minutes of lower extremity strength training, 15-20 minutes of endurance training, 15-20 minutes of timing and coordination training and a 5 minute cool-down for a total of 50-65 minutes of intervention. The timing and coordination training is based on principles of motor learning that enhance “skill” or smooth and automatic movement control.(16, 36-40) This program uses goal-oriented progressively more difficult stepping and walking patterns to promote the timing and coordination of stepping, integrated with the phases of the gait cycle.(16, 37, 38, 40) Conceptually, the exercise is intended to achieve its effects by shifting the center of pressure posteriolateral then forward, encouraging hip extension prior to stepping, loading the trailing limb, coordinating activation of the abductors of the soon to be swing leg with adductors of the stance limb, and shifting the center of pressure in medial stance to unload the stepping limb.(41-43) Progression is based on first separately increasing the speed, amplitude or accuracy of performance prior to undertaking a more complex task.(44) For example, the progression of stepping patterns is, 1) self-paced step forward and across, 2) increase stepping speed, 3) alternate side of stepping, 4) alternate forward with backward stepping. Walking patterns incorporate patterns of muscle coordination and interlimb timing similar to the stepping exercises into walking. Walking patterns progress by separately altering speed, amplitude (e.g. narrowing oval width), or accuracy of performance (e.g. without straying from the desired path), and then to complex walking patterns involving walking past others and with upper extremity object manipulation tasks added, such as carrying, bouncing or tossing a ball.(40) Timing and coordination training was used in both of our pilot studies.(30, 31) The

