#### **Outcomes representing components of the interventions (Secondary Outcomes):**

In order to assess the integrity of the intervention, we selected measures that represent the main components of the intervention (i.e. strength, endurance, flexibility, and timing and coordination) as our secondary outcomes. Measures representing the underlying components of the interventions are:

Lower Extremity Strength and Power - Leg strength will be measured by determining the 1 repetition maximum (1RM) for each leg individually using a Keiser A420 electronic pneumatic leg press machine. We will follow the protocol previously described by Callahan et al, 2007.(51) The maximum value observed on the A420 graphical display of either side will be recorded as the peak leg strength. Leg press power will also be

measured using the Keiser A420 leg press machine. Leg press power will be measured as the peak power graphically recorded when the individual performs a single leg press repetition pushing out as quickly as possible at 40% and 70% of 1RM. Five repetitions will be recorded for each leg at each resistance. The highest recorded power of all repetitions (either side, either resistance) will be recorded as leg press power.

Six Minute Walk Test (6MWT) - The Six Minute Walk Test (6MWT) of distance walked (meters) in six minutes, including time for rest as needed,(52) will be used to determine the impact of the exercise interventions on endurance. The 6MWT has been used to describe and monitor endurance capacity.(52) The 6MWT has established psychometric properties, test-retest reliability (Pearson  $r=.95$ ) in older adults,(48, 53) construct validity for graded exercise test and functional classification.(54) We chose the 6MWT because it is responsive to change,(55) widely used, and included in the NIH, PROMIS project to establish measures for clinical assessment. Greater distance covered during six minutes is better.

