### **10.1 Main Analysis.**

First, we will fit a series of linear mixed models using the SAS® MIXED procedure with change from baseline in each of the continuous outcome measures as the dependent variable; intervention arm (standard/standard plus), follow-up time point (12-/24-/36-week) and their interaction as fixed effects of interest; baseline value of outcome as a fixed-effect covariate; and a subject random effect to account for multiple follow-up assessments from the same patients over time and resulting stochastic non-independence of observations. We will appropriately construct means contrasts to compare the two intervention gains at 12 weeks (immediate effect), 24 weeks (delayed effect) and 36 weeks (sustained effect). Test of significance at  $\alpha=0.05$  for gait speed outcome at 12 weeks will be considered the formal test of the primary hypothesis 1.1. Second, we will repeat the above mixed models analysis entirely, but with stratification by baseline gait speed ( $<1.0/1.0+$  m/s). Tests of significance for gait speed outcome at 12 weeks in each of the two strata will be considered formal tests of the primary hypothesis 1.2. Statistical significance of at 24- and 36-week comparisons or other outcomes will be considered as formal tests of the secondary hypotheses involving activity and participation as well as delayed and sustained effects. Third, we will repeat the analyses after controlling for covariates identified a priori or found to be different between intervention arms by including them as additional fixed effects in supplements to main analyses.

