stratification by baseline gait speed (<1.0/1.0+ m/s). Statistical significance of 24- and 36-week means contrasts and other outcomes will be considered as tests of the secondary hypotheses involving process, activity and participation outcomes as well as persisting effects.

*Exploratory Analyses.* To examine subgroup-specific intervention effects, we will repeat the main analyses after stratification by various other baseline participant characteristics (besides baseline gait speed) to identify, if any, subgroups which are most/least likely to benefit from interventions. A priori, we anticipate that stratification by baseline walking confidence and cognitive function may show differential gains. We are aware that any definitive subgroup analyses should be supported by strong evidence in the form of a significant interaction effect. Tests of interaction generally have low statistical power, and it is not a main goal in the present trial to recruit a large number of participants required for definitive subgroup analyses beyond the already included pre-planned subgroups based on baseline walking speed. Thus, we plan to interpret our subgroup analyses with caution and an exploratory rather than a confirmatory philosophy, whose results are to be confirmed in a larger subsequent trial.

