#### **Final Statistical analysis plan (current, submitted manuscript)**

See published protocol for details. We compared baseline characteristics between groups using independent samples t-, chi-square and Fisher's exact tests. For main results, we performed an intention-to-treat analysis with multiple imputation for missing data. We fit linear mixed models with change from baseline in each continuous outcome measure as the dependent variable; intervention arm, follow-up time point and their interaction as fixed effects; baseline value of outcome as a fixed effect covariate; and a participant random effect. For outcomes based on accelerometers, wear time was an additional covariate. We constructed means contrasts to

compare the intervention gains at each of the follow-up time points. We repeated the analysis with gait speed stratum and stratum  $\times$  intervention as additional fixed effects to obtain stratum-specific findings. SAS® version 9.4 software (SAS Institute, Inc., Cary, NC) was used.

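### Section 1.2 predicts *similar* 12-week gains in strength, endurance and flexibility, but the plan states no criterion for similarity, only significance of a difference

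*Supplement*

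**What the plan says.** Section 1.2 makes two kinds of prediction for 12 weeks. For timing and coordination, activity and participation, Standard-Plus should gain more. For leg press strength and power, 6MWT and sit-and-reach it predicts no difference: gains in strength, endurance and "flexibility (Chair Sit-and-Reach) will be similar between the two active treatment groups". The next objective in 1.2 predicts greater gains in Standard-Plus at 24 and 36 weeks, so the similarity prediction belongs to 12 weeks only.

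Section 6.2.2 gives the purpose of these measures: "In order to assess the integrity of the intervention, we selected measures that represent the main components of the intervention".

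On analysis, section 10.1 fits one mixed model to every continuous outcome and states the rule for the secondary hypotheses: "Statistical significance of at 24- and 36-week comparisons or other outcomes will be considered as formal tests of the secondary hypotheses". The Main Analysis of the original statistical analysis plan, at the end of the supplement, has the same rule and names process outcomes: "Statistical significance of 24- and 36-week means contrasts and other outcomes will be considered as tests of the secondary hypotheses involving process, activity". The final statistical analysis plan refers to the published protocol for details and keeps the approach: "We fit linear mixed models with change from baseline in each continuous outcome measure as the dependent variable", with contrasts at each follow-up. None of the three deviations in the Summary of Changes concerns this point. Section 10.5.2 treats 6MWT as an outcome on which a difference is to be detected.

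**The concern.** A prediction of no difference needs its own decision rule: how large a difference still counts as similar, and how the data would exclude anything larger. The plan gives neither. If significance is the only yardstick, the similarity prediction survives whenever the contrast is non-significant, and it survives more easily the less precise the data are. Conversely, a difference too small to matter would refute it if it reached significance.

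The question is a live one for endurance. Standard-Plus sessions contain "15-20 minutes of endurance training, 15-20 minutes of timing and coordination training" (section 5.5), against 30-40 minutes of endurance training in the Standard arm (section 5.4). A between-arm difference in 6MWT is therefore possible, and a reader will want to know how large a difference the trial can rule out.

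**Working it through.** **Inputs.** From section 10.5.2: SD of 6MWT change 42.8 m, baseline SD 53.1 m, stated detectable difference 17.2 m with 80% power, 98 completers per arm at 36 weeks. From section 10.5: two-tailed tests at 0.05, and 55, 52 and 49 completers at 12, 24 and 36 weeks. These counts are per arm within stratum, since 2 × 49 = 98 matches section 10.5.2. At 12 weeks that gives 2 × 55 = 110 per arm.

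**The plan's own figure.** Detectable difference = SD × √(2/n) × (1.960 + 0.842) = 42.8 × √(2/98) × 2.802 = 17.1 m. Power for 17.2 m is 80%. The stated figure reproduces, as a test for a difference.

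**Precision at 12 weeks, unadjusted.** SE = 42.8 × √(2/110) = 5.77 m. The 95% CI half-width is 1.96 × 5.77 = 11.3 m.

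**Chance of a non-significant result when a difference exists.** P = Φ(1.96 − d/SE), the other tail being negligible.
- d = 12 m (an illustrative value): Φ(1.96 − 2.08) = 45%.
- d = 17.2 m: Φ(1.96 − 2.98) = 15%.

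**Allowing for baseline adjustment.** The planned model includes the baseline value. Assuming equal variances at baseline and follow-up, r = 1 − 42.8²/(2 × 53.1²) = 0.68 and the residual SD = 53.1 × √(1 − r²) = 39.2 m, so SE = 5.28 m.
- d = 12 m: Φ(1.96 − 2.27) = 38%.
- d = 17.2 m: Φ(1.96 − 3.26) = 10%.

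**Could the planned sample support an equivalence claim?** For two one-sided tests at 0.05 with a true difference of zero, power = 2Φ(margin/SE − 1.645) − 1. The documents give no margin, so those below are assumptions. They use the unadjusted SE of 5.77 m.

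| Assumed 6MWT margin | Power |
|---|---|
| 10 m | 7% |
| 15 m | 66% |
| 17.2 m | 82% |
| 20 m | 93% |
| 25 m | 99% |

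With the adjusted SE of 5.28 m, power is 89% at 17.2 m and 97% at 20 m.

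No SD is given for leg press strength, power or sit-and-reach, so the same calculation cannot be made in their units.

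**The case against.** The strongest reply is that nobody has said a non-significant result will be read as similarity. That is correct. A reader might infer that the investigators intend this, but no sentence says so. The list that completes the sentence in section 10.1 covers activity, participation, delayed and sustained effects, not the 12-week component outcomes. The wording that adds process outcomes is in the original analysis plan, and the final plan states no significance rule of its own. What stands is narrower: a hypothesis of similarity is stated, significance is the only criterion offered for secondary hypotheses, and nothing else could decide it.

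A reader might also infer that these outcomes are meant to prove that Standard-Plus gives up nothing in fitness. The documents do not say that. The stated purpose is to check the integrity of the intervention, and no equivalence or non-inferiority aim is declared.

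Nor should the halved treadmill time be taken as evidence of an endurance loss. Section 5.5 says walking and standing time is kept equal between arms. In the PRIME pilot (section 2.4), both groups improved on 6MWT although the timing-and-coordination arm lists strengthening but no endurance training. That makes similarity more credible. It does not establish it, because no between-arm 6MWT estimate is given.

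Finally, 17.2 m and 98 per arm belong to the 36-week hypothesis, where a greater gain is predicted and a difference test fits. Here 17.2 m serves only as a reference value and has no standing as an equivalence margin.

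**Conclusion.** The point holds as a missing criterion. The plan states a similarity hypothesis at 12 weeks for leg press strength and power, 6MWT and sit-and-reach, and offers only a difference test to judge it. Following the plan to the letter, similarity could be supported only by non-significance.

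For 6MWT, a true 12 m difference would go undetected about 38% to 45% of the time, and a 17.2 m difference about 10% to 15%. The lower figures assume that baseline adjustment brings the SD to about 39 m; the higher ones use the unadjusted SD of 42.8 m. All assume 110 completers per arm and a normal approximation, and make no allowance for multiple imputation.

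The matter is confined to one clause of one secondary hypothesis. The 12-week gait speed test, and the outcomes for which greater gains are predicted, are not affected.

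**What to change.** For these 12-week outcomes, report the adjusted between-arm difference with its 95% CI, and state that no conclusion of similarity will be drawn from p>0.05. This is the safest form and needs no new analysis.

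If a similarity claim is wanted, state and justify a margin for each outcome in its own units, and make the claim only if the 90% CI of the 12-week adjusted difference lies within it (two one-sided tests at 0.05). The final analysis plan is written after completion, so a margin set now must be labelled post hoc. For 6MWT the planned size makes this workable for margins of about 17 m or more. For the other outcomes, feasibility has to be judged from their own SDs.

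The cost is one paragraph, using contrasts that the model already produces. The downside is that *similar* becomes harder to claim.
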